#### Potential moderators of treatment efficacy

At baseline, demographic variables (e.g. age, gender), the duration of insomnia, and concomitant use of sleep medication will be documented as potential moderators of treatment efficacy. As further potential moderators, the following variables will be assessed at baseline: (a) patients’ chronotype, measured using the 13-item Composite Scale of Morningness (CSM; [54]; *α* = 0.84 [54] to 0.87 [55]); (b) treatment expectations and evaluations using the short form of the Patient Questionnaire on Therapy Expectation and Evaluation (PATHEV; [56]; *α* = 0.82 (Suitability) to 0.89 (Hope of Improvement), depending on subscale); (c) perceived usefulness of internet-delivered psychotherapy employing the Perceived Usefulness subscale of the ETAM ([31], 2017; *α* = 0.87); (d) patients’ perceptions of control over attending internet-delivered/face-to-face psychotherapy using the Perceived Behaviour Control subscales of the eTAP and TAP [50, 51]; (e) prior experiences with internet-delivered interventions/apps and face-to-face psychotherapy using five self-developed items; (f) attitudes towards treatment expectations using two self-developed items, each rated on a 4-point Likert scale; and (g) the degree to which patients feel informed about the characteristics of both intervention arms, utilising four self-developed items, each rated on a 4-point Likert scale (see Appendix 1 for further details about e, f, and g).

Moreover, therapists will briefly assess patients’ adherence to CBT-I after each session. They will also document the patient’s agreed bedtime window, which will be used to calculate adherence to bedtime restriction [57]. Finally, for health-economic analyses, therapists will document the time that they spent on each patient’s therapy (see Appendix 2 for details).

### Patient timeline {13}

Figure 1 shows the patient timeline.

### Sample size {14}

Since there is neither a validated non-inferiority margin for the insomnia treatment nor an established procedure for determining one, we followed the recommendation of the Delta2 group and considered different perspectives, including anchor-based clinical judgement and distribution-based reasoning to select the non-inferiority margin of the primary outcome (ISI) for this trial [58]. First, most clinicians involved in this trial agreed that new insomnia treatments are not inferior to the first-line treatment if the difference in post-intervention ISI scores is less than 2 points. Accordingly, 2 or more points were considered the minimally important difference (ISI range 0–28 points). From a distribution-based perspective, *d* = 0.5 is a commonly used lower limit for the smallest difference considered important [59], which corresponds to 2.3 points on the ISI. Second, as the non-inferiority margin should be smaller than the minimal important difference, 2 points on the ISI are an upper limit for the non-inferiority margin. Contrary to the minimal important difference, the non-inferiority margin should describe a clinically negligible difference. We agreed that the boundary between “minimal important” and “clinically negligible” is not sharply delineated, meaning that the boundary should not be set directly; for example, 0.1 points below the clinically relevant difference. There was no doubt that a 1-point difference is a clinically negligible difference. From a distribution-based perspective, 0.9 points correspond to a *d* = 0.2 (small) effect size according to Cohen’s taxonomy. Third, integrating these different perspectives, clinical and statistical arguments, with clinical reasoning being more important to us, a group difference δ of 1.5 points was conservatively considered clinically negligible and hence chosen as the non-inferiority margin. We intend to demonstrate non-inferiority of therapist-guided iCBT-I versus face-to-face CBT-I with regard to post-intervention ISI scores based on a shifted *t*-test at a one-sided significance level of 2.5%. To test for non-inferiority, the null hypothesis that ISI scores in the face-to-face CBT-I arm are ≥ 1.5 points higher than in the therapist-guided iCBT-I arm with an assumed common standard deviation of 4.5 points is rejected if the two-sided 95% confidence interval (CI) for the difference in ISI scores (control versus experimental) is < 1.5 points. To achieve 90% power, 382 patients must be included in analysis (191 per group; nQuery Advisor 7.0). Non-compliance and drop-out after randomisation are assumed to be no more than 10% [37]. Therefore, 422 patients will be randomised.

### Recruitment {15}

Several recruitment strategies are in place for achieving adequate patient enrolment. First, participating centres will recruit patients from their outpatient facilities. Second, press releases and established contacts with major German online and print media will be used to announce the trial. Interested subjects may visit the project website and provide their ZIP code. They will then be referred to the nearest study centre within 1-h travel distance of the patients’ residence, if possible. Third, recruitment will be supported by the German Sleep Society (DGSM) and the section Sleep Medicine of the German Association for Psychiatry, Psychotherapy and Psychosomatics (DGPPN).

## Assignment of interventions: allocation

### Sequence generation {16a}

Patients will be randomised to one of the two treatment arms with a 1:1 allocation ratio. Treatment allocation will be done centrally in the eCRF in REDCap® by the Clinical Trials Center (CTU) of the Medical Center—University of Freiburg. For each study centre, block randomisation with varying block sizes will be performed, with all group allocations concealed from the investigators to minimise selection bias.

### Concealment mechanism {16b}

The allocation sequence will be concealed until interventions are assigned as therapists randomise patients in the eCRF by clicking an icon.

### Implementation {16c}

The allocation sequence will be created centrally in the eCRF using the web-based data entry system REDCap® by the Clinical Trials Center (CTU) of the University of Freiburg Medical Center. Therapists at the study centres will enrol patients and assign them to the interventions by clicking on the “randomise” icon in the eCRF.

## Assignment of interventions: blinding

### Who will be blinded {17a}

Blinding of patients and therapists is impossible due to the specific characteristics of the interventions. Participating patients will be thoroughly informed about the study; hence, they will understand the treatment arm to which they have been assigned. Data analysts will not be blinded.

### Procedure for unblinding if needed {17b}

Not applicable due to the lack of blinding.

## Data collection and management

### Plans for assessment and collection of outcomes {18a}

Patient data will be collected in pseudonymised form with an electronic Case Report Form (eCRF) using REDCap®. Access to the eCRF will be granted to authorised study therapists and further members of the study team only, and only if they have received appropriate training in working with the system. In addition, a comprehensive manual will be provided. Study therapists will add new patients and document patients’ baseline data and further CBT-I session data in the eCRF. Data will be verified during data entry by built-in format and edit checks and so-called “data quality rules”. Patients will be invited automatically to online surveys to answer baseline, post-intervention, and follow-up questionnaires. In addition, sleep diary data will be collected. In the internet-delivered treatment, this will be done through a progressive, access-controlled web app. In the face-to-face treatment, patients will receive a folder containing a sleep diary in paper form. After completing the treatment, the sleep diary will be sent to the coordinating centre at the University of Freiburg Medical Center. Patient identification is ensured only by the study-specific pseudonym, not by the person’s name or any other personal data. Study team members will transfer the data into the eCRF. Details on the specific assessments and questionnaires can be found in Fig. 1 and in section “Outcomes {12}”.

### Plans to promote patient retention and complete follow-up {18b}

During recruitment, patients will receive detailed information about the requirements of study participation. To achieve high compliance, they will be randomised after completing the baseline questionnaire and directly before being able to participate in the intervention. Patients may discontinue participation in the intervention at any time without providing a reason or suffering any negative consequences. All study patients, including those who discontinue treatment, will be contacted via email and asked to complete the post-intervention and follow-up assessments. All questionnaires at all measurement points will be filled out using an online survey, providing a high level of flexibility and convenience for patients. Reminders for filling out the questionnaires will be sent automatically to individual patients who have not yet completed the questionnaires. To promote patient retention, we will employ the strategies for increasing response rates to questionnaires recommended in the Cochrane review conducted by Edwards et al. [60]. Given that a trial evaluating a previous version of the therapist-guided iCBT-I intervention showed a drop-out rate of 4.6% in the intervention group [37], non-compliance and drop-out are assumed to be no more than 10% in this trial. In the case of protocol deviations, as many outcomes as possible will be collected.

### Data management {19}

The setup of the eCRF and data management will be performed with REDCap®, which is developed and maintained by the REDCap® Consortium ([contact]). This system uses built-in security features to prevent unauthorised access to patient data, including an encrypted transport protocol for data transmission from the participating study centres to the study database. An audit trail provides a history of the data entered, changed, or deleted, indicating the processor and date. The study database is located on a server of the information technology facility (Zentrum für Digitalisierung und Informationstechnologie, ZDI) at University of Freiburg Medical Center. Employees of the Clinical Trials Unit charged with hosting the eCRF and the study database will be obliged to maintain data confidentiality and to comply with data-protection regulations. Access will be granted to authorised personnel only. Technical specifications of the database will be described in the codebook delivered automatically by the REDCap® system.

Before entering any data, the trial database and eCRFs will be validated. Study therapists and further members of the study team will not be granted access to the eCRF until they have been trained and have signed an access form. Data will be verified during data entry by built-in format and edit checks and data quality rules.

### Confidentiality {27}

All research data will be stored using a unique study identification code for each patient. The reference lists that link personal data with the study identification code will only be accessible to the respective participating study centres and securely stored on site. These lists will be deleted 10 years after data collection is complete (after the last patient has completed the final survey), by employees delegated for this purpose in a two-person review (= good clinical practice (GCP)-compliant). This timely deletion will be ensured by the study centres. Scientific evaluations will be carried out in a pseudonymised manner, and the results will not allow conclusions to be drawn about the patients’ identity. In scientific publications, study results will be presented in an anonymised format, ensuring that making any inferences about individuals is impossible.

### Plans for collection, laboratory evaluation and storage of biological specimens for genetic or molecular analysis in this trial/future use {33}

Not applicable because no biological specimens will be collected.

## Statistical methods

### Statistical methods for primary and secondary outcomes {20a}

#### Efficacy

The primary efficacy analysis will be performed in the per-protocol set, excluding patients with major protocol violations since it is generally recognised that “in an equivalence or non-inferiority trial, use of the full analysis set is generally not conservative” (European Medicines Agency—CPMP/ICH/363/96, Sect. 5.2.3, p. 26). For sensitivity analysis, the same analysis will be performed according to the intention-to-treat principle, based on the full analysis set, including all randomised patients with their original treatment allocation. The effects of internet-delivered and face-to-face CBT-I—with respect to the primary endpoint ISI at post-intervention—will be tested within a linear mixed model for repeated measures with corresponding two-sided 95% confidence intervals (CIs). The model will include treatment and study centre as independent variables. In cases involving low recruitment rates at specific centres, additional sensitivity analyses will be performed. The one-sided test of non-inferiority (internet-delivered versus face-to-face CBT-I) at a significance level of 2.5% will be based on the two-sided 95% CI from the mixed model for repeated measures. The null hypothesis will be rejected if the lower limit of the CI for the difference lies entirely above -1.5 points.

If non-inferiority is concluded, a test for superiority of therapist-guided iCBT-I versus face-to-face CBT-I will be conducted. For this, the primary analysis will be repeated in the full analysis set. If the resulting two-sided 95% CI lies entirely below zero, superiority of therapist-guided iCBT-I versus face-to-face CBT-I will be concluded. As this is a closed test procedure, it will not be necessary to adjust the significance level *α* (see “Points to consider on switching between superiority and non-inferiority” EMA—CPMP/EWP/482/99). Analysis in the mixed model for repeated measures will permit valid inferences under the “missing at random” assumption, which seems justified since we expect that most of the missing data will be absent for reasons probably unrelated to the missing outcomes. Secondary endpoints will be analysed in a fashion similar to the primary outcome, using regression models, as appropriate, for the respective type of data. Treatment effects will be calculated using two-sided 95% CI.

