### Intervention description {11a}

Both therapist-guided iCBT-I and face-to-face CBT-I are based on a published and widely used German-language CBT-I manual [33]. Thus, the two formats are identical in content and encompass the following CBT-I core components: (a) psychoeducation, (b) sleep restriction therapy, (c) stimulus control therapy, (d) cognitive therapy, and (e) relaxation techniques. Both formats consist of six sessions lasting 50 min each. The CBT-I components are delivered in the same order. In both groups, treatment is considered to be in accordance with the protocol if (1) at least 4 of the 6 scheduled sessions took place within the specified 10 weeks after randomisation, (2) no additional psychotherapeutic treatment was sought, and (3) there has been no increase in psychiatric medication. All therapists will be certified psychological or psychiatric psychotherapists for behavioural therapy with expertise in sleep medicine, or psychotherapy trainees supervised by certified psychological or psychiatric psychotherapists for behavioural therapy with expertise in sleep medicine, reflecting the current situation of insomnia treatment in Germany. All therapists will provide both treatments. To facilitate a standardised procedure and the equivalence of content, treatment manuals for both CBT-I conditions will be used by therapists, comprising templates and boilerplates (therapist-guided iCBT-I) and example formulations for psychoeducational information plus exercise sheets (face-to-face CBT-I). Table 1 summarises the content of the six sessions, which will be the same for both treatment conditions.

**Table 1 Tab1:** Session content of the face-to-face and therapist-guided iCBT-I

Session	Main objectives	Content / exercises
1. My good start	• Receiving an overview of the therapy (face-to-face or internet-delivered); defining therapy goals; learning about sleep and insomnia	• Psychoeducation on sleep & insomnia • Defining **p**recipitating, **p**redisposing, and **p**erpetuating factors (3-P model) • Learning sleep hygiene rules • Becoming familiar with the sleep diary (app) • Implementing small and larger relaxation activities in everyday life

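### Non-inferiority is decided on the per-protocol set alone, although its exclusions happen after randomisation and may be related to outcome; the full analysis set should have to agree

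*Protocol article*

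**What the plan says.** The Efficacy section {20a} sets the decision rule: "The primary efficacy analysis will be performed in the per-protocol set, excluding patients with major protocol violations". It then adds: "For sensitivity analysis, the same analysis will be performed according to the intention-to-treat principle, based on the full analysis set". The reason given is a regulatory guideline statement that the full analysis set is generally not conservative in a non-inferiority trial. The Discussion (Study contributions) repeats the argument and says that the trial, unlike its predecessors, is powered for the per-protocol sample. The full analysis set does decide one thing, the superiority test that follows if non-inferiority is concluded.

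The criteria for treatment according to protocol are in Intervention description {11a}: "at least 4 of the 6 scheduled sessions took place within the specified 10 weeks after randomisation", no additional psychotherapy, and no increase in psychiatric medication. The section on concomitant care {11d} removes from the per-protocol analysis anyone who begins other psychotherapy, or begins or increases psychiatric or sleep medication, during study participation.

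On blinding, section {17a} says: "Data analysts will not be blinded". It does not say who classifies protocol violations.

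**The concern.** A statement that the full set is not conservative is a reason not to rely on the full set alone. It does not show that the per-protocol set alone is conservative. That depends on who is excluded, and here every criterion is an event after randomisation.

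Seeking other psychotherapy or adding medication is a plausible reaction to a treatment that is not working. The session criterion also operates differently by arm. One arm completes platform sessions and gets written reminders; the other attends in person and is reminded by telephone or email ({11c}, Intervention description {11a}). The Limitations section itself expects therapists to be less practised in written guidance and says this might lower the efficacy of iCBT-I.

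If failing patients leave the iCBT-I arm's per-protocol set more often, the deciding analysis understates the deficit it is meant to rule out. As written, a full-set interval that failed to exclude the margin would carry no stated consequence.

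**Working it through.** **Inputs from Sample size {14}.** Margin 1.5 ISI points ("a group difference δ of 1.5 points was conservatively considered clinically negligible and hence chosen as the non-inferiority margin"); "an assumed common standard deviation of 4.5 points"; one-sided level 2.5%; power 90%; 382 analysed (191 per arm); 422 randomised (211 per arm); at most 10% non-compliance and drop-out. The true difference is not stated; 0 is assumed because it reproduces the stated size.

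**Reproducing the plan.** The normal approximation gives 190 per arm. With the noncentral t distribution, power is 0.8999 at 190 and 0.9014 at 191 per arm, so 191 per arm (382) is exact. For the inflation, 382/0.90 = 424.4, close to the stated 422 (422 × 0.90 = 379.8).

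**Bias formula.** Let p_i and p_c be the shares excluded from the iCBT-I and face-to-face arms, and g the ISI gap between excluded and retained patients, equal in both arms. Each arm's all-patient mean is its retained mean plus p × g, so

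per-protocol difference = all-patient difference − g × (p_i − p_c).

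With 211 randomised per arm, SE = 4.5 × √(1/[211(1 − p_i)] + 1/[211(1 − p_c)]). The chance of claiming non-inferiority is Φ((1.5 − per-protocol difference)/SE − 1.96).

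**False claims when the all-patient difference equals the margin (1.5 against iCBT-I).** The exclusion rates and gaps are assumptions, since the document gives none.

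| Excluded, iCBT-I v face-to-face | Gap g | Shift | False non-inferiority rate |
|---|---|---|---|
| 10% v 10% | 3, 5 or 7 | 0 | 2.5% |
| 12% v 8% | 5 | 0.20 | 6.3% |
| 15% v 10% | 5 | 0.25 | 7.7% |
| 15% v 5% | 3 | 0.30 | 9.5% |
| 20% v 10% | 5 | 0.50 | 18.2% |
| 15% v 5% | 5 | 0.50 | 19.0% |

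For the last row, SE = 4.5 × √(1/179.35 + 1/200.45) = 0.4625, and Φ(0.5/0.4625 − 1.96) = Φ(−0.879) = 0.190. The 12% v 8% and 15% v 5% rows keep the average exclusion at the protocol's own 10%.

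**The opposite imbalance.** With 5% v 15% excluded, g = 5 and no all-patient difference, the per-protocol difference is 0 + 0.5 = 0.5 against iCBT-I. Power is then Φ(1.0/0.4625 − 1.96) = Φ(0.202), about 58%.

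**Power if both sets must succeed, true difference 0 in each.**
- Per-protocol, 191 per arm: Φ(1.5/0.4605 − 1.96) = 0.903.
- Full set, 211 per arm with complete data: Φ(1.5/0.4381 − 1.96) = 0.928.
- Joint, bivariate normal with correlation √(382/422) = 0.951: 0.894.

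**Power if exclusions are differential.** With 15% v 5%, g = 5 and a per-protocol difference of 0, the full-set difference is 0.5. Full-set power is Φ(1.0/0.4381 − 1.96) = Φ(0.32), about 63%, and joint power cannot exceed that.

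**The case against.** The per-protocol choice is deliberate, justified in the text, and the trial is sized for it. The full-set analysis is pre-specified with the same model. The worry about the full set is also sound: if patients who add medication or psychotherapy improve as a result, the full set can hide treatment failure. The rates above are false-claim rates only if the all-patient difference is taken as the target. The plan would also make imbalance visible, since outcomes are sought regardless of adherence, violations are to be described, and drop-out is to be plotted by group ({18b}, {20c}). All of this stands. It supports keeping the per-protocol analysis, but not letting it decide alone.

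A reader might infer four stronger things that the document does not support:

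- That unblinded analysts assemble the per-protocol set. Section {17a} says only that analysts are unblinded. Most criteria are recorded facts (sessions attended, medication, other therapy), which limits discretion.
- That the full analysis set has no role. It is a planned sensitivity analysis and it decides superiority.
- That the rule favours iCBT-I. The direction is unknown. The one related figure, 4.6% drop-out in the intervention group of a trial of a previous version of the iCBT-I programme ({18b}), gives no support for heavier losses in that arm.
- That 19% is an estimate. It is the result of one assumed scenario.

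The statistical analysis plan is not shown. It may say how discordant results are read and how membership is fixed. The article nevertheless states which set is primary.

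**Conclusion.** The point holds as a weakness of the decision rule. Per-protocol as primary is a recognised choice. Per-protocol as the only basis for the claim is not shown to be conservative, because the exclusions follow randomisation and are plausibly related to outcome.

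On assumed figures (5-point gap, 12% v 8% to 15% v 5% excluded, all-patient difference at the margin), the false non-inferiority rate is about 6% to 19% instead of 2.5%. It stays at 2.5% with equal exclusions and equal gaps, and the opposite imbalance works against iCBT-I.

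There is a smaller point of definition. The term major protocol violations in {20a} is not tied to the criteria in {11a} and {11d}. Those two sections also differ: {11a} names an increase in psychiatric medication, while {11d} adds sleep medication and new starts, over study participation, which could run past the 10-week endpoint. In an open-label trial with a self-reported endpoint, membership of the deciding set should leave no room for choice. The change should be made before outcomes are compared by arm.

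**What to change.** 1. Keep the per-protocol analysis, but claim non-inferiority only if the 95% CI excludes a 1.5-point deficit for iCBT-I in both the per-protocol and the full analysis set.
2. State that per-protocol membership is classified from a listing without arm or post-baseline ISI and frozen before analysis, and amend the statement on analyst blinding in {17a} to fit.
3. Tie major protocol violations in {20a} to the criteria in {11a} and {11d}, and reconcile those two sections on medication and time window.

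**Cost.** Wording and masked arm codes. The full-set analysis and outcome collection regardless of adherence are already planned, and no extra patients are needed: with no true difference in either set, joint power is about 89% against 90%. The loss grows if exclusions differ between arms (full-set power about 63% when the full-set difference is 0.5). With complete outcome data, the rule brings the false-claim rate in the scenarios above back to at most 2.5%, because the full-set test itself has that level. It does not recover power lost when the imbalance runs against iCBT-I.

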#### Primary outcome

The primary study outcome will be insomnia severity at post-intervention, assessed using the Insomnia Severity Index (ISI; [27]), a questionnaire that is commonly used in insomnia research [20, 29, 38] and clinical care [15]. Insomnia severity will be assessed at all measurement points (baseline, post-intervention 10 weeks after randomisation, and follow-up 6 months after randomisation). The ISI questionnaire consists of seven items, each answered on a 5-point Likert scale with response options ranging from 0 to 4 and a total score ranging from 0 to 28. In several studies, the ISI has demonstrated good internal consistency with *α* ranging from 0.70 to 0.90 [27, 28, 39]. For all measurement points, total scores will be calculated.

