#### Health-economic evaluation

Quality-adjusted life years (QALYs) will be based on the AQoL-6D, which generates patient preference-based utilities on a scale of 0 (death) to 1 (perfect health), using the time-trade-off method [46]. QALY gains will be estimated by calculating the area under the curve (AUC) of linearly interpolated AQoL-6D utilities between measurement points to cover the follow-up period. Healthcare use, patient and family expenditures, and productivity losses will be self-assessed with the Trimbos and Institute for Medical Technology Assessment “Treatment Inventory of Costs in Patients with psychiatric disorders” questionnaire (TiC-P) and used for costing from a societal and public healthcare perspective.

For the health-economic evaluation, direct medical costs and costs due to absence from work or reduced efficiency during paid or unpaid work will be assessed at baseline and follow-up using the TiC-P [47, 48]. A list of unit cost prices will be utilised to compute healthcare costs on a per-participant basis [49]. The questionnaire’s test–retest reliability has been shown to be acceptable [48]. Budget impact will be presented as a difference in costs, with a comparison of various uptake levels of therapist-guided iCBT-I across different scenarios, estimating the expected change in healthcare system expenditures after different uptake levels of therapist-guided iCBT-I. The costs of healthcare of various intervention mixes (therapist-guided iCBT-I and face-to-face CBT-I) are compared with the *status quo*.

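### The primary model lists only treatment and centre; adding pre-randomisation baseline ISI would gain precision at no cost

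*Protocol article*

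**What the plan says.** The Efficacy part of section {20a} tests post-intervention ISI in a linear mixed model for repeated measures, first in the per-protocol set and then, as a sensitivity analysis, in the full analysis set. The superiority test repeats the same analysis in the full analysis set. On the model terms it says: "The model will include treatment and study centre as independent variables". It names no baseline, time or treatment-by-time term.

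The Primary outcome section has the ISI measured at baseline, 10 weeks and 6 months. On timing, section {18b} says of patients that "they will be randomised after completing the baseline questionnaire and directly before being able to participate in the intervention". Baseline ISI is therefore a pre-randomisation measurement.

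Two further statements in the Efficacy section bear on the point. The missing-at-random assumption is one "which seems justified since we expect that most of the missing data will be absent for reasons probably unrelated to the missing outcomes". And "Secondary endpoints will be analysed in a fashion similar to the primary outcome", with regression models suited to the type of data.

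**The concern.** The pre-treatment value of an outcome is usually among its strongest predictors. Leaving it out of the model puts the variance it explains into the residual and widens the interval that is compared with the margin. That matters here because the margin is tight: 1.5 points on a 28-point scale.

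Two features of this trial add to the case:

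- **Per-protocol primary analysis.** Patients leave this set because of post-randomisation events: too few sessions, other psychotherapy, or more psychiatric or sleep medication. Such events may depend on severity and may differ between an online and an in-person format. Randomisation does not guarantee balance in the set that remains, and the listed model has no term to correct a difference in baseline ISI.
- **Missing data.** If missingness depends on baseline severity, a model that uses baseline ISI accounts for it, whereas a model without it may not. Section {20c} plans to compare the baseline characteristics of patients with and without missing values, but the listed model would not use what that comparison finds.

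**Working it through.** **Inputs from the Sample size section:** margin 1.5, SD 4.5, one-sided 2.5%, 191 per arm analysed, 90% power.

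**Assumptions:** true difference 0 (the protocol expects only negligible differences); correlation r between baseline and post-treatment ISI of 0.3, 0.4 or 0.5. The protocol gives no r, so a range is shown.

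**1. The plan's own figure, without baseline**

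SE = 4.5 × √(2/191) = 0.4605. Non-centrality = 1.5 / 0.4605 = 3.257. With 380 degrees of freedom, the noncentral t distribution gives 90.1% power. 191 is the smallest number per arm that reaches 90%, so the stated 382 reproduces with no baseline adjustment. The 95% CI half-width is 1.96 × 0.4605 = 0.90 points.

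**2. With baseline ISI as a covariate**

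Residual SD = 4.5 × √(1 − r²). Half-width = 1.96 × residual SD × √(2/191). Power is calculated as in step 1. Equivalent unadjusted size per arm = 191 / (1 − r²).

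| r | Residual SD | Half-width | Power at 191 per arm | Equivalent unadjusted n per arm |
|---|---|---|---|---|
| 0 (as listed) | 4.50 | 0.90 | 90.1% | 191 |
| 0.3 | 4.29 | 0.86 | 92.6% | 210 |
| 0.4 | 4.12 | 0.83 | 94.4% | 227 |
| 0.5 | 3.90 | 0.78 | 96.3% | 255 |

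**3. Missingness that depends on baseline**

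A large-sample simulation used one post-treatment value per patient, r of 0.3 or 0.5, and about 8% to 9% missing. The log-odds of missingness rose by 0.5 per SD of baseline in one arm; the slope in the other arm was varied.

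| Slope in other arm | Bias without baseline, r = 0.3 | Bias without baseline, r = 0.5 |
|---|---|---|
| 0.5 (same mechanism) | none beyond simulation error | none beyond simulation error |
| 0 | 0.06 points | 0.10 points |
| −0.5 | 0.11 points | 0.21 points |

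The baseline-adjusted estimate was unbiased to within simulation error (about 0.01) in every case. The largest bias is 0.21 / 1.5 = 14% of the margin, and it needs opposite mechanisms in the two arms.

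**The case against.** The strongest reply is that the sentence says which variables the model will include, not that it includes no others. The list is visibly incomplete: a repeated-measures model aimed at the post-intervention visit needs time and treatment-by-time terms, and neither is named. A treatment main effect alone across all visits would not give that contrast. Baseline ISI may also be one of the repeated responses, since baseline is one of the three measurement points. With the time terms, that would recover most of the loss. This stands as a possible reading, and it is why the point is an improvement and not an error. It does not settle the matter, because the text does not say that baseline is a response.

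Other objections also stand:

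- **Power.** A reader might infer that the trial is underpowered or the test invalid. The documents do not support that: the 90% power reproduces without adjustment.
- **Missing at random.** A reader might infer that the assumption fails. It need not: bias arose only when baseline-related missingness differed between arms, and it was small against the margin. Section {20c} also plans descriptive checks of drop-out and missing values.
- **Per-protocol set.** Adjustment corrects imbalance in baseline ISI only. It does not restore the comparability that randomisation gave.
- **Economic analysis.** A reader might infer that QALYs and costs will be compared unadjusted. The protocol says how QALYs are computed ("QALY gains will be estimated by calculating the area under the curve (AUC) of linearly interpolated AQoL-6D utilities") and that two multilevel models will be fitted, but it lists no covariates for them. Nothing follows from that silence.

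**Conclusion.** The point holds as a free improvement to the primary model. As listed, the model leaves out a predictor that is already collected before randomisation. At an assumed r of 0.3 to 0.5, naming it would cut the half-width by 0.04 to 0.12 points and add about 2.5 to 6 percentage points of power at 191 per arm. The size rests on that assumed correlation and on a true difference of 0. It also assumes that baseline ISI is not already in the response vector with the time terms; if it is, most of the gain is already there and only the wording needs completing. Protection against baseline-related missingness is a small further benefit. Correction of baseline ISI imbalance in the per-protocol set is another, limited to that one variable.

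**What to change.** State in the protocol or SAP, before the data are analysed, how baseline ISI enters the primary model. Either of these will do:

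- baseline ISI as a fixed covariate, with visit, treatment-by-visit and baseline-by-visit terms beside treatment and centre, and the treatment contrast taken at 10 weeks; or
- baseline ISI as a response with the arm means constrained to be equal at baseline, plus the visit and treatment-by-visit terms.

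Use the same specification in the per-protocol non-inferiority analysis, the full-analysis-set analysis and the superiority test. For secondary outcomes analysed in the same way, use the baseline value of each outcome. Since the data analysts are not blinded, the choice should be dated before they work with outcome data.

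The cost is wording only: the data are already collected, and the sample size need not change.
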